## Abstract

**Background:**

Nodal staging is a major concern in colorectal cancer as it is an important prognostic factor. Several techniques that could potentially improve patient treatment and prognosis have been developed to increase the accuracy of nodal staging. Sentinel lymph node detection has been shown to accurately reflect nodal status in various tumors and has become the standard procedure in nodal staging of breast cancer and melanoma. However, in colorectal cancer, sentinel lymph node detection techniques are still controversial as the sensitivity reported in the literature varies from one study to another. Recently, indocyanine green fluorescence–guided surgery has been reported to be a useful technique for detection of macroscopic and microscopic metastatic deposits in lymph nodes after intravenous administration of indocyanine green dye. However, no studies have focused on the potential role of sentinel lymph node detection after systemic administration of indocyanine green dye, so-called systemic sentinel lymph nodes, or on the correspondence between the identification of the sentinel lymph node by standard local injection techniques and the detection of fluorescent lymph nodes with this new approach.

**Objective:**

The aim of this protocol is to validate the concept of sentinel lymph nodes identified by fluorescence imaging after intravenous injection of indocyanine green dye and to compare the sentinel lymph nodes identified by fluorescence imaging with sentinel lymph nodes detected by the standard blue dye technique.

**Methods:**

This study (SeLyNoFI; Sentinel Lymph Nodes Fluorescence Imaging) is a diagnostic, single-arm, open-label feasibility study, including patients with colorectal adenocarcinoma with or without metastatic disease who are admitted for elective colorectal resection of the primary tumor. This study evaluates the feasibility of a new approach for improving the accuracy of nodal staging using fluorescence imaging after intravenous administration of indocyanine green dye. Sensitivity, positive predictive value, and accuracy of the classical blue dye technique and of the investigatory fluorescence imaging technique will be calculated. Translational research will be proposed, if applicable.

**Results:**

As of June 2020, this study has been registered. Submission for ethical review is planned for September 2020.

**Conclusions:**

The potential correlation between the two different approaches to detect sentinel lymph nodes offers new strategies for improving the accuracy of nodal staging in colorectal cancer. This new concept of the systemic sentinel lymph node and a greater understanding of the interactions between systemic sentinel lymph nodes and standard sentinel lymph nodes may provide important information regarding the underlying mechanism of primary tumor lymphatic drainage. The enhanced permeability and retention effect can also play a role in the fluorescence of systemic sentinel lymph nodes, especially if these lymph nodes are inflamed. In this case, we can even imagine that this new technique will highlight more instances of lymph node–positive colorectal cancer.

**International Registered Report Identifier (IRRID):**

PRR1-10.2196/17976

## Introduction

Colorectal cancer represents a major cause of cancer-related mortality worldwide [1]. Nodal staging in colorectal cancer is of major concern as patients with stage III cancer, which is defined by nodal metastases at pathology, should receive adjuvant chemotherapy [2]. Sentinel lymph node analysis has been shown to accurately reflect nodal status in various tumors and sentinel lymph node detection techniques have become the standard of care in breast cancer and malignant melanoma where unnecessary lymphadenectomy can be avoided in patients with negative nodal status [3,4]. Sentinel lymph node detection was introduced for colorectal cancer in the early 2000s [5,6]. The aim of sentinel lymph node detection in colorectal cancer is not to identify the need for lymphadenectomy—this is already systematically performed during surgery—but to identify the first tumor draining node and focus on more advanced techniques during histopathological analysis to improve the accuracy of nodal staging. Despite some encouraging results, the technique has not been widely used. This is probably due to the fact that data reported in the literature have provided mixed results [5,7]. The poor performance of classical sentinel lymph node detection techniques using intra- or peritumoral injections in colorectal cancer could be related to two factors. The first is that, in patients with locally advanced tumors, draining lymphatic channels could be obstructed by the tumor, leading to false negative results [5]. The second is that mesenteric drainage is more heterogeneous when compared with cutaneous or subcutaneous region drainage, such as those involved in breast cancer or in melanoma, potentially leading to missed metastases [8]. For this reason, there may be discordance between the first lymph node, which anatomically drains the tumor and which is detected after peritumoral injection, defined classically as the *sentinel lymph node*, and lymph nodes invaded by cancer cells and detected after intravenous injection that we have defined as the *systemic sentinel lymph node*.

Recently, indocyanine green–fluorescence imaging has emerged as a potential technique for the detection of sentinel lymph nodes after peritumoral injection [9-11]. The preliminary results of studies [12-15] using peritumoral injection of indocyanine green dye for sentinel lymph node detection in colorectal cancer were encouraging, but we recently reported the results of a pilot study [16] which were disappointing in terms of accuracy and sensitivity.

New approaches are thus required. Recently, we published our observations on using fluorescence imaging after intravenous injection of indocyanine green dye to detect lymph node metastatic deposits both ex vivo and in vivo in colorectal cancer [17]. We confirmed these findings in a recent retrospective study [18] evaluating 12 patients who underwent colonic resection, for peritoneal metastasis detection after intravenous injection. Moreover, we observed that primary colonic tumors were more fluorescent than surrounding tissue upon fluorescence imaging after intravenous injection of indocyanine green dye.

Therefore, we hypothesized that ex vivo fluorescence imaging after intravenous injection of indocyanine green dye could represent a new approach for improving nodal staging through detection of fluorescent lymph nodes on the operative specimen. Furthermore, we hypothesized that these lymph nodes, identified after intravenous injection of indocyanine green dye and defined as systemic sentinel lymph nodes, when compared with classical anatomical tumor-draining sentinel lymph nodes, could represent a lymph node subset that is more sensitive to nodal invasion, thus serving as a more appropriate target for advanced histopathological analyses. The pathophysiological mechanism is 3-fold: first, in patients with large tumors, involved lymph nodes will be more fluorescent; second, in patients with small tumors, the fact that primary colonic tumors accumulate indocyanine green dye and that the dye is progressively cleared from the tumor by lymphatic drainage should allow the lymph node draining the tumor to be highlighted (Figure 1); and third, regarding the enhanced permeability and retention effect, we can consider that inflamed or reactive lymph nodes accumulate more indocyanine green dye and become more fluorescent [19]. This is very interesting considering that reactive lymph nodes present more risk to be invaded and are thus a key target for extensive histopathological analyses [19].

**Figure 1 figure1:**
[figure not shown]
Illustrations of the systemic sentinel lymph node hypotheses. In patients with small tumors, we expect to find a correlation between the blue sentinel lymph node and the systemic lymph node. In patients with large tumors, we expected to have a false negative blue sentinel lymph node and a true positive systemic lymph node. FI: fluorescence imaging; ICG: indocyanine green.

The primary objective of the SeLyNoFI study is to assess the feasibility of metastatic lymph node detection in colorectal cancer by ex vivo fluorescence imaging after intravenous administration of indocyanine green dye. In this study, we will evaluate the sensitivity, specificity, and accuracy of the technique for determining nodal status, both intraoperatively (entire fresh specimen imaging) and in the pathology department (fixed specimens).

The secondary objectives are to correlate the results of the fluorescent sentinel lymph node detection technique after intravenous injection of indocyanine green dye with sentinel lymph node detection by the standard blue dye technique, to study the link between the local lymphatic drainage pathway (classical tumor-draining sentinel lymph nodes) and the systemic pathway (systemic sentinel lymph nodes). Finally, we will evaluate the tumor-to-background fluorescence ratio of the primary colonic tumor.

## Methods

### Study Design

The SeLyNoFI study is designed as a single-arm, 2-step (monomulticentric), academic, prospective observational-interventional study conducted by the Department of Surgical Oncology at the Institute Jules Bordet of the *Université Libre de Bruxelles* in Brussels. It will start as a monocentric, 2-stage (Simon procedure) study and will be followed by a multicentric study (among members of the International Research Institutes network) if the null hypothesis that the sensitivity of the indocyanine green–fluorescence imaging technique is lower than 60% (*p*_0_, sensitivity obtained by the classical blue dye technique improved by 10%) can be rejected based on the data generated in the monocentric study (*p*_1_, power calculated in case of a true sensitivity of 90%). To assess the feasibility of this technique, all cases will be included, even under conditions in which the technique might be expected to be unreliable (eg, long delay between injection of indocyanine green dye and fluorescence assessment). However, if the null hypothesis cannot be rejected after the monocentric phase, further development will be halted (Figure 2).

**Figure 2 figure2:**
[figure not shown]
Flowchart of the study. CAE: carcinoembryonic antigen; CT: computed tomography; FDG-PET/CT: 18-Fluoro-deoxy-glucose positron emission tomography with computed tomography; MRI: magnetic resonance imaging.

### Population

#### First Step (Monocentric)

To determine the sample size of the study, we used the 2-stage Simon procedure (minimax design) [20]. The first stage requires a small sample size (n_1_) and determines the threshold r_1_ as the number of successes (ie, TP_1_, the number of true positives) above which the trial’s second stage can begin. If that number is not surpassed (TP_1_<r_1_), then the trial ends at the end of the first step.

Once the second stage has begun, the total sample size, including those already enrolled in stage 1, is defined (n_tot_=n_1_+n_2_), and the second threshold r_tot_ for the number of successes (TP_1_+TP_2_) is defined. If the total number of successes surpasses the threshold (TP_1_+TP_2_>r_tot_), the monocentric study can terminate, and the indocyanine green dye technique will be considered worthy of further evaluation in the multicentric study. If the number of successes is not surpassed after (TP_1_+TP_2_<r_tot_ for n_tot_ cases), then the trial will terminate, and the technique will be considered inadequate and abandoned.

With *p*_0_= 60% and a *p*_1_=90%, the sample size needed in the first stage is n_1_=8 (lymph node–positive N1 or N2) and the number of successes (true positive) to surpass is r_1_=5. The total sample size needed is n_tot_=17 (lymph node–positive patients) with a total number of successes r_tot_=14 (with α=.05 and β=.10). As the prevalence of patients with N1, N2, or N3 is estimated to be 50%, the number of patients needed for enrollment in stage 1 and 2 are about 16 and 34, respectively.

Based on the number of patients treated at the Institute Jules Bordet, the time necessary to execute this step is estimated to be 1 year.

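### The final Simon threshold of 14 out of 17, read as a number to be surpassed, gives 76% power rather than the stated 90%; the matching threshold is 13

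*Protocol article*

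**What the plan says.** All of the design is in the Protocol article, First Step (Monocentric), with its rationale under Study Design.

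- Method: "we used the 2-stage Simon procedure (minimax design").
- Stage 1: "With *p*_0_= 60% and a *p*_1_=90%, the sample size needed in the first stage is n_1_=8", counted in node-positive patients, and "the number of successes (true positive) to surpass is r_1_=5".
- Final look: 17 node-positive patients in all, "with a total number of successes r_tot_=14 (with α=.05 and β=.10").
- Go rule: "If the total number of successes surpasses the threshold (TP_1_+TP_2_>r_tot_), the monocentric study can terminate", and the technique moves to the multicentric step.
- Stop rule at stage 1: "If that number is not surpassed (TP_1_<r_1_), then the trial ends at the end of the first step". The final stop rule has the same form: in words the threshold is not surpassed, and in brackets the total is below r_tot.
- Consequence: under Study Design, if the null hypothesis cannot be rejected after the monocentric phase, development is halted.

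**The concern.** In a Simon design the threshold r can be written in two ways: as the largest count that still fails (go if more than r), or as the smallest count that succeeds (go if at least r). The two differ by one patient. The section uses the first convention throughout its definitions, and r1=5 fits it. The value r_tot=14 looks as if it belongs to the second.

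The stake is the only gate between the monocentric and the multicentric step. If the threshold is one too high, a technique that performs as hoped is abandoned more often than the plan says. The bracketed inequalities add to the problem, because a count equal to the threshold meets neither the '>' of the go rule nor the '<' of the stop rule.

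**Working it through.** **Inputs** (First Step (Monocentric) and Study Design): p0=0.60, p1=0.90, α=.05, β=.10, n1=8, r1=5, n_tot=17, r_tot=14. Stage 2 therefore adds 17−8=9 patients.

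**Formula.** With X1 ~ Bin(8, p) and X2 ~ Bin(9, p),

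P(go) = Σ over x=6, 7, 8 of P(X1=x) × P(X2 > r_tot − x).

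At p=0.60 this is the type I error, and at p=0.90 the power.

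**1. The printed rule: more than 5 of 8, then more than 14 of 17**

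| x | P(X1=x), p=.90 | P(X2>14−x), p=.90 | product | P(X1=x), p=.60 | P(X2>14−x), p=.60 | product |
|---|---|---|---|---|---|---|
| 6 | 0.1488 | 0.3874 | 0.0577 | 0.2090 | 0.0101 | 0.0021 |
| 7 | 0.3826 | 0.7748 | 0.2965 | 0.0896 | 0.0705 | 0.0063 |
| 8 | 0.4305 | 0.9470 | 0.4077 | 0.0168 | 0.2318 | 0.0039 |
| Sum | | | **0.7618** | | | **0.0123** |

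(Products and sums are from unrounded values.) The stated β=.10 is not reproduced: β = 1 − 0.7618 = 0.238.

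**2. Threshold 13 under the same convention: more than 5 of 8, then more than 13 of 17**

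| x | P(X2>13−x), p=.90 | product | P(X2>13−x), p=.60 | product |
|---|---|---|---|---|
| 6 | 0.7748 | 0.1153 | 0.0705 | 0.0147 |
| 7 | 0.9470 | 0.3624 | 0.2318 | 0.0208 |
| 8 | 0.9917 | 0.4269 | 0.4826 | 0.0081 |
| Sum | | **0.9045** | | **0.0436** |

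Both stated error rates are met.

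**3. Which design did the plan intend?** A full search over (n1, r1, n, r) with type I error ≤0.05 and power ≥0.90 gives 17 as the smallest total. Among designs of that size, the smallest expected sample size under p0 belongs to n1=8, r1=5, n=17, r=13, in the more-than convention. Its early-stopping probability under p0 is 0.6846, so the expected size is 8 + 9 × (1 − 0.6846) = 10.8. Three of the four printed numbers match this design; r_tot alone differs, by one.

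**4. Can another reading of stage 1 rescue 14 with '>'?** No. After exactly 5 of 8 the largest possible total is 5+9=14, which cannot exceed 14. Continuing on 5 or more leaves both figures at 0.0123 and 0.7618. A single-stage test of more than 14 of 17 has the same power, 0.7618.

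**5. Counts equal to the threshold**

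- *14 of 17.* The probability of passing stage 1 and ending on exactly 14 is the difference between the two rules: 0.9045 − 0.7618 = 0.143 at p=0.90.
- *5 of 8.* Under the printed final rule, treating this count as stop or continue changes nothing (step 4). With at least 14 of 17 required, continuing on 5 gives 0.0464 and 0.9174, against 0.0436 and 0.9045 when stopping. Both pairs are within the stated α and β.

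**The case against.** **The calculation is probably sound and only the notation slipped.** The sentence giving 5 calls it the number to surpass, whereas the sentence giving 14 calls it only a total number of successes. If 14 is the number required, the stated α and β are met. That is the likely origin, though it remains an inference. It does not rescue the text, because the same section defines r_tot with the word for exceeding and with '>'. Applied as printed, the rule fails 14 of 17.

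**The error is conservative.** This stands in part: type I error falls to 0.012 and no patient numbers change. But the plan states β=.10, and the cost is a false stop.

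**Figure 3 may show the right cut-offs.** It is not available, and its caption speaks of true-positive patients required, so it may give minimum counts. A correct figure would lower the risk of misjudging 14 of 17, but it would then disagree with the text.

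**A reader might infer that ties at both looks have no verdict.** The document does not support that. The words of both stop rules say that a threshold not surpassed means stopping, so 5 of 8 and 14 of 17 are failures in words. Only the bracketed '<' signs leave them open. The defect is a conflict between words and symbols. The 76% figure itself rests on the words, since it counts 14 of 17 as a failure.

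**Conclusion.** The point holds. As printed, the go/no-go rule has type I error 0.012 and power 0.762 at 90% sensitivity, against the stated .05 and 90%. The chance of abandoning a technique with the hoped-for sensitivity is 24%, more than twice the stated 10%. The threshold that fits the other printed numbers is 13 under the surpass convention, with 0.044 and 0.905.

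The disagreement between words and symbols is secondary. It matters at 14 of 17, the outcome that separates the two rules and has probability 14% at 90% sensitivity. At 5 of 8 it does not affect whether the stated error rates are met; it would affect only whether stage 2 recruitment goes ahead.

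The figures assume independent patients with a common sensitivity, exactly 8 and then 17 node-positive patients at the two looks, and one success counted per patient. It does not follow that the sample size is too small or that type I error is inflated: 17 node-positive patients suffice for the stated rates once the threshold is corrected.

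**What to change.** In First Step (Monocentric):

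1. Set r_tot=13 and keep '>'. Writing that at least 14 of 17 are needed is the same rule; use one convention for both looks.
2. Replace '<' by '≤' in both stop conditions, so that stage 1 stops at 5 or fewer of 8 and the final look fails at 13 or fewer of 17.
3. Check that Figure 3 shows the same cut-offs.
4. State the achieved operating characteristics: type I error 0.044 and power 0.905 at 90% sensitivity.

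If more than 14 of 17 is really intended, keep r_tot=14, still correct the inequality signs, and restate α as 0.012 and power as 0.76.

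The cost is one number, two inequality signs and one sentence, with no extra patients. The rule should be settled before the stage 2 results are known, so that a result of 14 of 17 is not interpreted after the fact.

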#### Second Step (Multicentric)

As the primary aim of this study is not to prove a hypothesis but to estimate parameters (sensitivity and ratio of fluorescent to nonfluorescent lymph nodes), sample size planning may be based upon the expected width of the confidence intervals [21]. In this study, in order to estimate a sensitivity of 95% with a 5% precision, we need a total sample size of 73 (lymph node–positive patients) to get a 95% confidence interval with a half-length of 5%. If the true sensitivity is 90% (ie, *p*_1_ for our Simon design), the precision will be 7% rather than 5%. As the prevalence of patients with N1, N2, or N3 is estimated to be 50%, the total number of patients needed is about 146. At least two other centers of the *Pole Hospitalier Universitaire de Bruxelles* network will be included (Figure 3).

The general overview of the study is shown in Figure 4.

**Figure 3 figure3:**
[figure not shown]
Decision diagram for 2-step study plan. True-positive patients required in stage 1 and stage 2 of the monocentric study to proceed to the multicentric study (step 2). P: patients; TP: true positive.

**Figure 4 figure4:**
[figure not shown]
Flow of samples through the study. After indocyanine green and blue dye injection, all lymph nodes removed during colectomy will be analysed for indocyanine green fluorescence and blue dye positivity, followed by pathologic analysis. Lymph nodes that are negative by initial pathology will be further examined by serial sectioning. ICG: indocyanine green; IHC: immunohistochemistry; LN: lymph node.

### Inclusion Criteria

Patients with biopsy-proven primary or metastatic colorectal cancer admitted for elective surgery of the primary colorectal tumor and who provide written informed consent will be included.

### Exclusion Criteria

Patients who are younger than 18 years old; are unable to give informed consent; have a history of allergy or hypersensitivity to investigational product (active substance or ingredients), to iodine, or to shellfish; have apparent hyperthyroidism, autonomous thyroid adenoma, unifocal, multifocal, or disseminated autonomy of the thyroid gland; have documented coronary disease or advanced renal insufficiency (creatinine >1.5 mg/dL); are on concurrent medication which reduces or increases the elimination of indocyanine green dye (ie, anticonvulsants, haloperidol, and heparin) during the 2 weeks before the expected operation; are pregnant; or are breastfeeding will be excluded.

### Preoperative Work-up and Surgery

All patients will undergo standard work-up including laboratory testing for tumoral carcinoembryonic antigen, thoraco-abdominopelvic computed tomography (CT), and abdominal magnetic resonance imaging (MRI), as necessary (eg, in patients with renal insufficiency). Patients with suspected metastases will undergo 18F-fluorodeoxyglucose positron emission tomography with computed tomography (FDG-PET/CT). Patients will undergo laparoscopy or laparotomy following the standard procedures for colectomy.

### Tracer Preparation

Indocyanine green dye (Pulsion Medical Systems SE) will be diluted with 10 mL of sterile water (2 mg/mL), and a dose of 0.25 mg/kg will be administrated by slow intravenous injection by central venous catheter at the beginning of the surgical procedure.

### In the Operating Room

#### Fluorescence Imaging

After colonic and rectal resection (as necessary), the operative specimen will be placed on a back table and the mesentery exposed. Fluorescence imaging is carried out with a dedicated near-infrared camera system. A light-emitting diode light source set to a wavelength of 760 nm is used, and the detector is a charge-coupled device (CCD) camera with a filter set to detect light with a wavelength of <820 nm. The fluorescent signal is sent to a digital video processor to be displayed on a monitor in real time. Videos will be recorded on a personal computer using a standard high-definition video program. The camera will be held directly by the surgeon at a distance of approximately 20 cm from the operative specimen. During fluorescence imaging exploration, hyperfluorescent lymph nodes will be marked with a green stitch. Thereafter, the colon will be opened, and primary tumors will be imaged for their fluorescence.

